#### Feasibility and Acceptability (Aim 1)

Feasibility will be assessed across 4 domains: screening, recruitment, retention, and intervention.

Screening feasibility refers to the practicality and efficiency of identifying eligible participants from the target population. Screening feasibility measures in our study include the total number of patients screened for eligibility, the proportion of screened patients who are eligible (eligibility rate), reasons for exclusion, and the number of individuals who must be screened to identify one eligible patient.

Recruitment feasibility evaluates the ability of the study team to successfully enroll eligible participants into the trial within the planned timeframe, using the planned recruitment methods. Recruitment feasibility measures in the Text4HF trial include the number of potential participants invited to participate in the study, those who declined participation, and those who provided informed consent; the percentage of eligible patients who consented (enrollment rate); the percentage of consented patients who provided consent, completed the baseline assessment, and were randomized (randomization rate); the time required to achieve the target sample size (expressed in months); and the number of participants enrolled per month (accrual rate).

Retention feasibility refers to the ability to keep enrolled participants in the study until the planned outcome assessments are completed. Retention feasibility is assessed in our trial by the proportion of randomized participants who remain in the study and complete the final follow-up assessment (completion rate). Additional measures of retention include the proportion of participants who voluntarily withdraw from the study (withdrawal rate) and the proportion of participants who are lost to follow-up (LTFU rate).

Intervention feasibility refers to the extent to which the TM intervention is delivered and received as intended by the study protocol. Intervention feasibility is assessed using 2 measures. The first measure is the percentage of TM successfully delivered, as determined by reports generated by the intervention delivery system (iCardia). The second measure is a self-report administered at the end of the intervention, which asks participants approximately how many of the study TM messages they received and read (none, some, about half, nearly all, or all).

Acceptability is assessed with an exit survey completed by all participants in the intervention group. The exit survey was developed solely for the purpose of this study and was adapted from the Technology Acceptance Model [82]. We designed a 23-question self-reported survey involving 19 Likert scale questions and 4 open-ended free text questions. The questions gather information such as perceived usefulness, satisfaction, and intention to continue receiving TM. The open-ended questions focus on features of the TM intervention that participants liked or disliked.

#### Patient-Reported Health Outcome Measures (Aim 2)

The primary outcome of interest is HF self-care, assessed with the SCHFI version 7.2 [46] at baseline, 4 weeks, and 12 weeks. The SCHFI (29 items) has 3 subscales: Self-Care Maintenance (10 items), Symptom Perception (11 items), and Self-Care Management (8 items). Standardized scores in the SCHFI range from 0 to 100. A total score of 70 or more indicates adequate self-care [13,73].

Secondary patient-reported health outcomes include medication and refill adherence (ARMS), heart-healthy diet adherence (SDBHF), HF knowledge (Atlanta Heart Failure Knowledge Test [AHFKT]), health-related quality of life (Minnesota Living with Heart Failure Questionnaire [MLHFQ]), self-efficacy (Self-Care Self-Efficacy [SCSE]), and health beliefs (BDCS, BMCS, and BSMS) at baseline, 4 weeks, and 12 weeks.

As part of the safety protocol, the study team will review the EHR and record adverse events, serious adverse events, and unanticipated problems, including unplanned hospitalizations, emergency department visits, and mortality or death events for all enrolled participants.

#### Demographics and Clinical Characteristics

Data collected will be a combination of self-reported information and data abstracted from electronic medical records. Demographic information includes the following (eg, name, date of birth, employment status, insurance, ethnicity, race, and education). Contact information includes address, telephone number, email address, HF clinical characteristics, such as New York Heart Association classification and left ventricular ejection fraction, will also be collected, along with medical history, past medical conditions and illnesses, medications, and hospitalizations. The Patient Health Questionnaire [80,81] (8 items) will be used to assess depression status. Comorbid conditions will be collected and scored using the Charlson Comorbidity Index [77-79] (which includes 19 comorbidities).

### Statistical Analysis Plan

#### Sample Size Justification for a Pilot RCT

Given the pilot nature of this RCT, the sample size was not based on a formal-efficacy-powered calculation. Instead, it was determined based on feasibility considerations and estimation of preliminary outcome variability. The main objectives of the study are to evaluate the feasibility, acceptability, and preliminary effects of the Text4HF intervention and to generate estimates of variability and effect sizes to inform a future, fully powered trial. The primary patient-reported outcome is HF self-care, measured using the SCHFI, which yields continuous scale scores and can be used to estimate between-group differences, variability, and effect sizes for a future definitive trial. Consistent with recommendations for pilot RCTs involving continuous behavioral outcomes [83,84], we determined that we need to enroll 30 participants and randomize them equally between study arms (n=15 per group) to inform a 90% powered trial with an expected standardized effect size in the medium range (0.3≤*d*<.7) [84]. This sample size is appropriate for estimating feasibility parameters, retention, intervention acceptability, and preliminary changes in SCHFI scores, while also providing estimates of SCHFI variability and effect size needed to design a future fully powered trial. Assuming up to 20% attrition over 12 weeks, approximately 24 participants are expected to complete the 12-week follow-up assessment. The target sample size also balances methodological recommendations for pilot RCTs with the available study resources, timeline, and anticipated recruitment capacity.

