#### Analysis Plan

The primary analyses comparing the intervention and usual care groups will follow the intention-to-treat principle, whereby participants are analyzed according to the group to which they were originally randomized, regardless of intervention adherence or exposure.

Standard descriptive statistics will be used to describe recruitment and retention rates, participant characteristics, and intervention acceptability. Chi-square tests and *t* tests will be used to examine differences between the groups in exploratory patient-reported outcomes (Table 2). Cohen *d* effect sizes will be used to evaluate the preliminary effect of the text messages on HF self-care measures as assessed by the SCHFI (Table 2). The significance level will be set at less than .05 for all analyses.

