## Discussion

### Anticipated Findings

Although TM has demonstrated effectiveness in self-management interventions, such as diabetes, hypertension, and obesity, evidence as a standalone study in individuals with HF is limited. Many of these studies on self-management are deployed in conjunction with remote patient monitoring. The Text4HF trial aims to address an important gap in the literature by providing preliminary evidence on the feasibility and efficacy of individually tailored text messages as a standalone intervention for improving self-care in middle-aged and older adult patients with HF. Given the potential for scalability, reach, and low cost of TM, this approach could evolve into a paradigm shift where TM could be deployed in an HF clinic. The study is not powered to establish efficacy; rather, it is intended to generate estimates of effect size and variability that will inform the design of a future fully powered RCT. We anticipate the study will demonstrate feasibility with recruitment and retention rates greater than 80%. Acceptability will be demonstrated with high rates of patient satisfaction and preliminary improvements in HF self-care compared with usual care.

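### Thirty participants cannot supply the effect size that the plan says is needed to design the definitive trial; they can supply the SD and the feasibility parameters

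*Protocol article*

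**What the plan says.** The section Sample Size Justification for a Pilot RCT says that the number was not derived from an efficacy power calculation but from feasibility and from the wish to estimate outcome variability. It then fixes the size from cited pilot-trial recommendations: "we determined that we need to enroll 30 participants and randomize them equally between study arms (n=15 per group"). The later trial's planning inputs are given as "to inform a 90% powered trial" and "with an expected standardized effect size in the medium range (0.3≤*d*<.7"). On dropout it says: "Assuming up to 20% attrition over 12 weeks, approximately 24 participants are expected to complete the 12-week follow-up assessment".

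The same paragraph adds a second yield. The sample is called appropriate for feasibility, retention, acceptability and preliminary change, "while also providing estimates of SCHFI variability and effect size needed to design a future fully powered trial". The Discussion (Anticipated Findings) repeats this straight after conceding that the study is not powered for efficacy: "it is intended to generate estimates of effect size and variability that will inform the design of a future fully powered RCT". The Analysis Plan names the statistic, in that Cohen d "effect sizes will be used to evaluate the preliminary effect of the text messages on HF self-care measures as assessed by the SCHFI", and sets the test level: "The significance level will be set at less than .05 for all analyses".

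**The concern.** Two claims are joined in one sentence, and only one of them holds. A pilot of this size estimates a standard deviation tolerably well. It does not estimate a standardized between-group difference well enough to choose a later sample size, because the required size varies with 1/d² and the uncertainty in d here is larger than the range of values under discussion.

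This matters because informing a definitive trial is the study's declared purpose. A reader who takes the sentence at its word could put the observed d into a sample-size formula. An estimate that is high by chance would then give a trial that is too small. One that is low or negative by chance could lead to an intervention being dropped.

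The point concerns a positive statement in the article. It does not rest on detail that a separate analysis plan might hold.

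**Working it through.** **Inputs.** From the sample-size section: 30 enrolled, 15 per arm, up to 20% attrition, 90% power for the later trial, expected d from 0.3 to below 0.7. From the Analysis Plan: Cohen d between groups on the SCHFI, level .05. Assumptions: two-sided testing in the later trial (sidedness is not stated), equal arms, normal outcomes, d from follow-up scores without baseline adjustment.

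**Step 1. The plan's own figure.** 30 × (1 − 0.20) = 24, or 12 per arm. It reproduces.

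**Step 2. Is 15 per arm a sensible pilot size?** Take d as known, estimate only the SD, and minimise pilot plus main-trial size at 90% power. The optimum is 19, 12 and 9 per arm for d = 0.3, 0.5 and 0.7. Fifteen lies within that range, although this check does not reproduce it exactly. The 95% limits for the true SD are 0.79 to 1.35 times the estimate with 15 per arm (28 df) and 0.77 to 1.42 times with 12 per arm (22 df). This reasoning supports the SD claim. It takes d as given, so it does not support the effect-size claim.

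**Step 3. Precision of d.** SE(d) = √(2/n + d²/(4n)), with n per arm. At d = 0.5:

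- n = 15: √(0.1333 + 0.0042) = 0.371; half-width 1.96 × 0.371 = 0.73; interval -0.23 to 1.23.
- n = 12: √(0.1667 + 0.0052) = 0.415; half-width 1.96 × 0.415 = 0.81; interval -0.31 to 1.31.

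Intervals from the non-central t distribution agree to within 0.01. The assumed band is 0.7 − 0.3 = 0.4 wide, so the half-width alone exceeds it. In 400,000 simulated pilots per scenario with true d = 0.5, the observed d fell inside the band about 36% of the time with 12 per arm and 41% with 15. With 12 per arm it was zero or negative in 23%, 11% and 4% of pilots for true d = 0.3, 0.5 and 0.7.

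**Step 4. What the band means for the later trial.** Size per arm = 2(1.96 + 1.2816)²/d² = 21.02/d², rounded up: 234 (d = 0.3), 85 (d = 0.5), 43 (d = 0.7). The pilot estimate can hardly separate these.

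**Step 5. Conditional consequence.** Suppose the later trial is sized for 90% power on the observed d. Its true power is Φ(d√(n/2) − 1.96), with n now the later trial's size per arm. For example, if d is observed as 0.7 and is truly 0.5, n = 43 and power = Φ(0.5 × √21.5 − 1.96) = Φ(0.36), about 64%. Power falls below 80% once the observed d exceeds the true d by a factor of about (1.96 + 1.2816)/(1.96 + 0.8416) = 1.16. Among simulated pilots with observed d > 0:

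| True d | Power < 80%, 12 per arm | Power < 80%, 15 per arm |
|---|---|---|
| 0.3 | 60% | 57% |
| 0.5 | 48% | 46% |
| 0.7 | 43% | 40% |

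**Step 6. Sensitivity to baseline adjustment.** The document gives no baseline-to-follow-up correlation r. Adjustment would multiply the half-width by roughly √(1 − r²). For assumed r of 0.3, 0.5 and 0.7 the factors are 0.95, 0.87 and 0.71. The half-width becomes about 0.78, 0.70 and 0.58 with 12 per arm, and 0.69, 0.63 and 0.52 with 15. All remain above 0.4.

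**The case against.** The strongest reply is that the document never says the later trial will be sized on the pilot's d alone. It speaks of informing the design and lists variability, retention and recruitment beside effect size. It says that the study is not powered for efficacy, calls the patient-reported outcomes exploratory, and in Limitations asks for cautious reading of the preliminary effect. How a later trial is sized belongs in that trial's protocol.

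Much of this stands, and it rules out several stronger readings that a reader might infer:

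- *The plan leads to an underpowered definitive trial.* Not supported. The Step 5 figures hold only under a sizing rule that the document does not contain.
- *The later trial's power would be about 50%.* This confuses the chance of falling below 80% power with the power itself. With 12 per arm, true d = 0.5 and observed d > 0, the later trial's true power has a median of about 83% and a mean of about 73%.
- *Assuming a range for d and then estimating d is circular.* Choosing a sample from a planning range and then estimating the quantity is ordinary design. The valid point is only that the rule supports the SD and not d.
- *Thirty is too few.* Step 2 does not support this for a pilot.

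What the reply does not remove is the claim itself. The sample-size section calls the effect size needed for the design, and the Discussion's caveat about efficacy is followed in the same sentence by the statement that the study will generate that effect size. General caution about interpreting results does not say what the estimate may be used for.

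**Conclusion.** The point holds as a should-fix. The article credits 30 participants with an effect-size estimate fit for designing the definitive trial, and the sample cannot deliver it. The 95% half-width for d is about 0.73 (15 per arm) to 0.81 (12 per arm), the interval around 0.5 includes zero, and it spans far more than the whole 0.3 to 0.7 range. That conclusion needs only the plan's own numbers and the usual normal, equal-arm assumptions, and it survives every assumed correlation tried for baseline adjustment.

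The underpowering percentages are conditional. They need the later trial to be sized on the pilot's positive point estimate, with two-sided .05 and 90% power. The sample size, the attrition arithmetic and the use of the pilot for the SD and feasibility parameters are sound.

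**What to change.** 1. In Sample Size Justification for a Pilot RCT and in Anticipated Findings, limit what the pilot contributes to the later design to SCHFI variability, retention, recruitment and acceptability.
2. In the same places, state that the definitive trial will be sized on a justified minimum important difference in SCHFI score and not on the pilot's observed d. The document gives no such difference, so its value is left for the investigators to justify.
3. In the Analysis Plan, state that Cohen d will be reported with its 95% confidence interval and as descriptive only.

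The cost is a few sentences and a slightly less favourable account of what the pilot yields. With 26 of 30 participants already randomized, nothing in enrollment, conduct or data collection has to change.

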#### Analysis Plan

The primary analyses comparing the intervention and usual care groups will follow the intention-to-treat principle, whereby participants are analyzed according to the group to which they were originally randomized, regardless of intervention adherence or exposure.

Standard descriptive statistics will be used to describe recruitment and retention rates, participant characteristics, and intervention acceptability. Chi-square tests and *t* tests will be used to examine differences between the groups in exploratory patient-reported outcomes (Table 2). Cohen *d* effect sizes will be used to evaluate the preliminary effect of the text messages on HF self-care measures as assessed by the SCHFI (Table 2). The significance level will be set at less than .05 for all analyses.

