### Randomization and Allocation Concealment

Following the completion of baseline assessments, enrolled participants are randomized in a 1:1 ratio to either the intervention or control group (n=15 per arm). The randomization sequence is preprogrammed in REDCap (Vanderbilt University) [47] using permuted block randomization stratified by age. Allocation concealment is maintained through a secure, blinded assignment process implemented within the REDCap system. Participants are randomized sequentially in the order in which they complete the baseline assessments. To preserve the integrity of the randomization process, the REDCap system prevents any attempt to change participant assignments following allocation.

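### The planned between-group t test does not adjust for baseline score or the age stratum and does not model weeks 4 and 12 jointly, so the pilot's effect estimate is less precise than its data allow

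*Protocol article*

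**What the plan says.** The Analysis Plan section gives the between-group method in one sentence: chi-square and t "tests will be used to examine differences between the groups in exploratory patient-reported outcomes (Table 2"). For self-care it adds that Cohen d "effect sizes will be used to evaluate the preliminary effect of the text messages on HF self-care measures as assessed by the SCHFI". On alpha it says "The significance level will be set at less than .05 for all analyses". No covariate, stratum term or repeated-measures model is named. The section does not say whether the t test is on the raw score or on change, or at which visit.

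The design offers more than this analysis uses. The Randomization and Allocation Concealment section allocates "using permuted block randomization stratified by age". Table 2 and the Patient-Reported Health Outcome Measures section schedule every patient-reported outcome at baseline, 4 weeks and 12 weeks.

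On numbers, the sample size section states that "we need to enroll 30 participants and randomize them equally between study arms (n=15 per group) to inform a 90% powered trial" and then: "Assuming up to 20% attrition over 12 weeks, approximately 24 participants are expected to complete the 12-week follow-up assessment". The same section lists estimates of variability and effect size for a future trial among the main objectives.

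**The concern.** The stated analysis does not match the design. Randomization is stratified by age, but a two-sample t test carries no stratum term. A baseline score is collected for each outcome, but the test does not adjust for it. Two follow-up visits are collected, but they can at most be tested one at a time.

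This matters because the SCHFI difference and its variability are products that the pilot is meant to hand to the next trial. With 12 to 15 participants per arm, the arms can easily differ at baseline by chance, and part of such a difference carries into an unadjusted week-12 comparison and its Cohen d. Adjustment removes that part and usually narrows the interval. What is at stake is precision, not the validity of the test.

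**Working it through.** **Inputs from the document.** 30 randomized 1:1, so 15 per arm; attrition up to 20%; alpha .05 (sidedness not stated; two-sided taken here); expected standardized effect from 0.3 to below 0.7.

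**Assumptions.** The correlation r between baseline and week-12 score within arm is not given; the range 0.3 to 0.7 is used. Completers split equally. The SD is the same at both visits. Age enters as one term (the cut points are not given); it is charged its degree of freedom and credited with no gain.

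**The plan's own figure.** 30 × (1 − 0.20) = 24 completers, so 12 per arm. This reproduces the stated 24.

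**95% CI half-width of the standardized week-12 difference, n = 12 per arm**

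- t test on the raw score: t(0.975, 22) × √(2/12) = 0.847.
- ANCOVA on baseline plus one age term: t(0.975, 20) × √[(2/12)(1 − r²)(1 + 2/19)].
- t test on change: t(0.975, 22) × √[(2/12) × 2(1 − r)].

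| Analysis | r = 0.3 | r = 0.5 | r = 0.7 |
|---|---|---|---|
| t test, raw score | 0.85 | 0.85 | 0.85 |
| t test, change score | 1.00 | 0.85 | 0.66 |
| ANCOVA, baseline only | 0.83 | 0.75 | 0.62 |
| ANCOVA, baseline and one age term | 0.85 | 0.78 | 0.64 |

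Against the raw t test, the last row is no narrower at r = 0.3, about 8% narrower at 0.5 (0.775/0.847 = 0.915) and about 25% narrower at 0.7 (0.639/0.847 = 0.754). If all 15 per arm were retained, the t test gives 0.75 and the same ANCOVA gives 0.74, 0.68 and 0.56.

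**Chance imbalance at baseline, 15 per arm.** The SD of the difference in baseline means is √(2/15) = 0.365 SD. The chance of a difference above 0.3 SD in either direction is 41%. Only r times the imbalance is expected to carry into the week-12 difference. To carry over more than 0.3 SD, the imbalance must exceed 0.3/r:

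- r = 0.3: above 1.00 SD, probability about 0.6%
- r = 0.5: above 0.60 SD, about 10%
- r = 0.7: above 0.43 SD, about 24%

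**What Cohen d would mean.** The SD of change is √[2(1 − r)] times the raw SD: 1.18 times at r = 0.3 and 0.77 times at r = 0.7. The same mean effect of 0.5 raw SD would therefore be reported on the change scale as 0.5/1.18 = 0.42 or 0.5/0.77 = 0.65. The document does not say which SD is used.

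**The case against.** The patient-reported outcomes are called exploratory, the Discussion says the trial is not powered for efficacy, and the Limitations section asks for cautious interpretation. A t test in a randomized comparison is valid, and its interval already allows for chance imbalance. The gain from adjustment depends on an unstated correlation and disappears at r = 0.3. All of this stands, and it limits the point to one of efficiency. It does not remove the point, because a good estimate of effect and variability is a stated purpose of the pilot.

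A reader might infer more than the document supports:

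- *The baseline score is thrown away.* Not established. The sample size section speaks of changes in SCHFI, and a t test on change would use baseline. That would not rescue the plan: it is no narrower than the raw t test at r of 0.5 or below, and it still ignores the stratum.
- *The week-4 data are thrown away.* Not established. Table 2 lists week 4, and a separate test at each visit is possible. What is missing is joint use of the visits.
- *Intention-to-treat becomes a completer analysis.* This is an inference about missing-data handling. The plan's definition is that "participants are analyzed according to the group to which they were originally randomized, regardless of intervention adherence or exposure", which a t test does not contradict. Rules for missing outcomes may sit in a full protocol or SAP that is not shown. Also, 20% is the plan's upper limit on attrition, and the Discussion anticipates retention above 80%.
- *A 41% chance of a misleading effect size.* The 41% is the chance of a baseline difference above 0.3 SD, not of an error of that size in the result.
- *Ignoring the stratum biases the result.* Ignoring a prognostic stratum typically makes the standard error too large, which is conservative. Nothing in the document shows that age predicts SCHFI.

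**Conclusion.** The point holds as a matter of precision. The document fixes a two-sample t test where the design supports an adjusted comparison. With 12 completers per arm, the half-width of 0.85 SD would fall to about 0.78 SD at r = 0.5 and 0.64 SD at r = 0.7, and would not change at r = 0.3. These figures rest on the assumed r, equal completion in the two arms and a single age term. They are for ANCOVA; any further gain from adding week 4 in a mixed model was not computed.

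The planned test is not invalid and no stated figure is wrong. The interval stays wide under either method, as expected in a pilot of this size. The change is worth making because it costs almost nothing and improves an estimate that the next trial will rely on.

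**What to change.** For the continuous scale scores, replace the t test with one of these:

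- ANCOVA of the week-12 score on arm, baseline score and age stratum; or
- a linear mixed model of the week-4 and week-12 scores with arm, visit, arm by visit, baseline score by visit and age stratum. This also uses week-4 data from participants who leave later, though not from anyone with no follow-up score.

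Name week 12 as the time point. Report the adjusted difference with its 95% CI as the main estimate. Derive the standardized effect from that difference and a stated SD, so that the future trial knows what scale it is on. Reporting the observed baseline-to-week-12 correlation would also help to plan that trial.

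The cost is one or two degrees of freedom and a change of analysis wording. No new data are needed, and the planned software, SPSS, fits both models. The Results section reports 26 of 30 participants randomized and gives no outcome comparison, so the wording can be settled before the groups are compared.

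### Plain Cohen d is named for the SCHFI effect passed to the next trial; at 22 to 28 degrees of freedom it overstates the effect by about 3% to 4%, which Hedges g removes at no cost

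*Protocol article*

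**What the plan says.** The Analysis Plan section compares the groups with chi-square and t tests and names Cohen d as the effect measure for self-care; these "effect sizes will be used to evaluate the preliminary effect of the text messages on HF self-care measures as assessed by the SCHFI". No correction for small samples is mentioned.

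The section Sample Size Justification for a Pilot RCT says what the number is for. The pilot is to supply "estimates of SCHFI variability and effect size needed to design a future fully powered trial", and the design is meant "to inform a 90% powered trial with an expected standardized effect size in the medium range" (d from 0.3 to below 0.7). Anticipated Findings, in the Discussion, repeats that effect size and variability will inform a later, fully powered trial.

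On numbers, the plan is to "enroll 30 participants and randomize them equally between study arms (n=15 per group"). It adds: "Assuming up to 20% attrition over 12 weeks, approximately 24 participants are expected to complete the 12-week follow-up assessment".

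**The concern.** Cohen d divides the difference in means by a sample SD. In small groups the expected value of one over the sample SD exceeds one over the true SD, so d is on average too far from zero. This is a systematic error in one direction. It is separate from the wide confidence interval that any 30-person pilot will have, and reporting that interval does not remove it.

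The bias would matter little if d were only descriptive. Here producing an effect size for the definitive trial is a stated aim. An effect size that is too large gives a definitive trial that is too small for its intended 90% power.

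**Working it through.** **Inputs**
- Randomised: 30, in a 1:1 ratio, 15 per arm (sample size and randomisation sections). df = 30 - 2 = 28.
- Completers: 20% attrition gives 30 x (1 - 0.20) = 24, which reproduces the article's figure. df = 24 - 2 = 22, however the losses fall between arms.
- Future trial: 90% power, d from 0.3 to below 0.7 (sample size section).
- Significance level: 0.05 (Analysis Plan). Sidedness is not stated; two-sided is assumed.
- For illustration, true d = 0.5, inside the article's range.

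**Step 1. Bias of plain d.** The correction factor is J = 1 - 3/(4df - 1), and the expected value of d is the true value divided by J.

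| Analysed | df | J | Overstatement, 1/J - 1 |
|---|---|---|---|
| 30 | 28 | 1 - 3/111 = 0.9730 | 2.8% |
| 24 | 22 | 1 - 3/87 = 0.9655 | 3.6% |

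The exact gamma-function factors are 0.9729 and 0.9655. Simulation at d = 0.5 gave overstatements of 2.8% with 15 per arm and 3.7% with 12 per arm. If only the 26 participants enrolled so far were analysed (df = 24), the figure would be 3.3%.

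**Step 2. Effect on the next trial's size.** The required n per arm is 2(1.960 + 1.282)²/d², so it varies as 1/d². Using d/J in place of d multiplies n by J².
- Shortfall against the correct size, 1 - J²: 5.3% at 28 df and 6.8% at 22 df.
- The same gap as extra sample needed on top of the undersized trial, 1/J² - 1: 5.6% and 7.3%.
- At d = 0.5 the correct size is 85 per arm. The biased values 0.514 and 0.518 give 80 and 79 per arm.

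**Step 3. Effect on its power.** Power is approximately Φ(3.24 x J - 1.96), where 3.24 = 1.960 + 1.282.
- 28 df: 0.884.
- 22 df: 0.879.

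A nominal 90% becomes about 88%.

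**Step 4. Bias beside the pilot's own uncertainty.** At d = 0.5 with n per arm, SE(d) = √(2/n + d²/(4n)).
- n = 15: SE = 0.371, bias = 0.014, ratio 0.037.
- n = 12: SE = 0.415, bias = 0.018, ratio 0.043.

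The bias is about 4% of one standard error.

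**The case against.** **The bias is immaterial in a pilot.** It is about 0.04 of a standard error. The article's own expected range of 0.3 to 0.7 is far wider than a shift of 3% to 4%, and its Limitations section asks for caution with the preliminary effects. The 88% figure also assumes that the next trial is sized on the pilot's point estimate, with that estimate at its expected value. The article does not commit to this; it also lists raw between-group differences and variability as inputs. All of this stands, and it keeps the point minor. It does not make plain d the better choice, because the correction costs nothing.

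**The absence of a correction is inferred.** The article is silent on it, and a fuller plan may apply one. That is fair. Still, the measure named is Cohen d, and its natural reading is the uncorrected statistic.

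**A stronger reading that the documents do not support.** The sample size section speaks of "preliminary changes in SCHFI scores", while the Analysis Plan speaks of SCHFI measures. A reader might infer that the two sections conflict over whether d is standardised by the SD of change or of follow-up scores. They do not: in the Analysis Plan, measures most naturally means the SCHFI scales, as its pointer to Table 2 indicates. Which score and SD lie behind d is a detail that a condensed article commonly leaves to the full plan.

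A reader might go on to infer a large loss of power. With equal SDs and no baseline difference, change-score d equals follow-up d times 1/√(2(1 - r)), where r is the baseline-to-follow-up correlation. The article gives no r. The shift is -15% at r = 0.3, zero at r = 0.5 and +29% at r = 0.7, so even its direction is unknown. At r = 0.7, a follow-up d of 0.5 becomes 0.645 and the trial would have 51 per arm, with about 71% power if analysed on unadjusted follow-up scores. That needs both the assumed correlation and a mismatch between sizing and analysis that the article nowhere describes. If the definitive trial is analysed on change, 51 per arm keeps 90%. If it adjusts for baseline, about 85 x (1 - 0.49) = 43.35, or 44 per arm, is enough.

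**Conclusion.** The point holds as a minor, free improvement. Plain Cohen d, as named, overstates the standardised SCHFI effect by 2.8% with 30 analysed and 3.6% with 24. Carried unchanged into the definitive trial's sample size, this means a sample about 5% to 7% too small and power of about 88% instead of 90%.

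The overstatement rests on the article's own sample sizes and on the usual normal-theory model with equal SDs. The consequences for the next trial assume in addition a two-sided 0.05 level and sizing on the pilot's d. Chance error in a pilot of this size is far larger than the bias. Nothing here shows a contradiction in the article, and a change-score effect size would not be wrong for a trial analysed on change.

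**What to change.** In the Analysis Plan section, replace Cohen d with Hedges g, defined as d multiplied by 1 - 3/(4df - 1), with df the number analysed in the two arms minus 2. The multiplier is 0.973 with 30 analysed and 0.966 with 24.

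As a clarification only, the same sentence could name the score (12-week or change) and the SD used, so that the definitive trial can be sized to match its own analysis.

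The cost is one sentence and a one-line calculation, with no new data. Reported effect sizes become about 3% smaller. The article reports 26 of 30 enrolled and expects completion in June 2026, so the change can be made before the final analysis.
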